## Abstract

**Background:**

Brain metastases often occur in cancer evolution. They are not only responsible for death but also for disorders affecting the quality of life and the cognitive functions.

Management of brain metastases usually consists in multi-modality treatments, including neurosurgery, whole brain radiotherapy (WBRT), and more recently radiosurgery (SRS) or fractionated stereotactic radiotherapy (FSRT), systemic treatment (chemotherapy or targeted therapy), combined or not with corticosteroids. Almost 20% of brain metastases can present recent (within 15 days) bleeding signs on neuro-imagery. In these conditions, WBRT is the usual treatment. Yet, patients may benefit from a more aggressive strategy with SRT or FSRT. However, these options were suspected to possibly major the risk of brain haemorrhage, although no scientifically proven. Radiation oncologists therefore usually remain reluctant to deliver SRS/FSRT for bleeding brain metastases.

It is therefore challenging to establish a standard of care for the treatment of bleeding brain metastases.

We propose a phase II trial to simultaneously assess safety and efficacy of FSRT to manage brain metastases with hemorrhagic signal.

**Methods:**

The STEREO-HBM study is a multicenter two-step non-randomised phase II trial addressing patients with at least one bleeding brain metastasis out of a maximum of 3 brain metastases. Each brain metastasis will be treated with 30 Gy in 3 fractions for 1 week.

The main endpoint is based on both safety and efficacy endpoints as proposed by Bryant and Day’s design. Safety endpoint is defined as the rate of bleeding complications 4 months post-FSRT while efficacy endpoint is defined as the 6-month local control rate. Multi-modal MRI will be used to assess intra-tumoral hemorrhagic events before and after treatment. Patients’ quality of life will also be assessed.

**Discussion:**

Management of bleeding brain metastases is still debated and poorly explored in clinical trials. There is sparse and weak data on the signification of pretreatment intra-tumour haemorrhagic signs or on the risk of brain bleeding complications after FSRT.

We expect this first prospective phase 2 trial in this particular setting will allow to clarify the place of FSRT to optimally manage bleeding brain metastases.

**Trial registration:**

NCT 03696680, registered October, 4, 2018.

**Protocol version:**

Version 2.1 dated from 2018/11/09.

## Background

Brain metastases occur in 20–40% of cancer patients. They represent the most common manifestation of intracranial malignancy [1]. They are an important cause of mortality and morbidity. Indeed, brain metastases can result in devastating clinical consequences, such as sensitive-motor defect, cognitive disturbance, social relationship deterioration. Without any specific treatment, patients with brain metastases usually survive for 1 to 2 months [2, 3]. For these patients with brain evolution of their cancer, death results from the extra-cerebral disease progression in most of cases, but from complications related to brain lesions progression in at least 25–50% of cases [4, 5].

Brain metastases exhibit highly variable revelations modes. They can be asymptomatic or otherwise occur more abruptly. An epileptic seizure or loss of consciousness may reveal brain damage. In that latter case, it is estimated that 1.9 to 10% of these symptoms are associated with intra-tumoral haemorrhage [6]. Bleeding risk varies depending on histology. For example, melanoma metastases are macroscopically bleeding in 35.7% of cases, whereas 2.9 and 4.7% of metastases from adenocarcinoma or anaplastic carcinoma are bleeding, respectively [7]. Overall, almost 20% of brain metastases can present recent (within 15 days) bleeding signs on neuro-imaging (Magnetic Resonance Imaging (MRI) or Scan).

Although radiosurgery (SRS) or fractionated stereotactic radiotherapy (FSRT) is now the mainstay of treatment for brain oligo-metastases (3–5 metastases), allowing a 12-month local control greater than 75% [8], whole brain radiotherapy (WBRT) still remains the usual treatment of haemorrhagic brain metastases, despite its poor efficacy, namely a 6-month and 12-month local control rate of 37 and 15%, respectively [9]. This attitude is consistent with the report of the French High Authority of Health (HAS) which does not support radiosurgery for the treatment of haemorrhagic brain metastases (HAS report 2001). It is based on the results from a retrospective study (131 metastases on 54 patients) [10]: haemorrhage was identified in 7.4% of the metastases before radiosurgery and in 18.5% of the metastases after radiosurgery. Since this publication, although it did not clearly demonstrate a relationship between radiosurgery and the risk of haemorrhage, FSRT/SRS is suspected to increase the risk of brain haemorrhage. Furthermore, in spite of several reports of intra-tumor haemorrhage after radiosurgery of brain metastases, radiosurgery was not shown to increase the incidence of haemorrhage. Thus, among melanoma patients carrying brain metastases [11], the rate of intra-tumor haemorrhage was shown to be similar before and after treatment by stereotactic Gammaknife (23.7% vs. 15.2%, *p* = 0.89); the presence of intra-tumoral bleeding before treatment was not found to major the risk of bleeding after treatment (*p* = 0.9). According to some authors, the occurrence of post-treatment bleeding would not be related to the achievement of radiosurgery, but rather to the intrinsic sensitivity of the tumor to bleed [12].

Besides these conflicting findings, it has to be highlighted that most of these studies were conducted exclusively with SRS (a single fraction issued) and from either a Gammaknife® or a linear adapted accelerator. To date, there are no specific available data for FSRT (several fractions) with Cyberknife®, a newer technology.

Overall, radiation oncologists generally remain reluctant to deliver FSRT on hemorrhagic brain metastases. Therefore, the standard treatment remains panencephalic irradiation, even if it is clearly not optimal.

In this context, there is a real need to establish a standard management of hemorrhagic brain metastases, notably using more innovative radiotherapy techniques like FSRT.

In order to specifically document the interest of FSRT in the management of hemorrhagic brain metastases, we propose the first non-randomized phase 2 prospective trial aiming to simultaneously evaluate safety and efficacy of this treatment. In addition, it will accurately document, using multi-modal MRI, intra-tumoral hemorrhagic events before and after treatment. Patients’ quality of life before and after treatment will be also assessed.

## Methods/design

### Trial objectives

#### Primary objective

The main objective is based on joint primary endpoints of safety and efficacy of FSRT for patients with bleeding brain metastases at diagnosis, as proposed by the Bryant-and-Day design [13].

The safety endpoint is the rate of hemorrhagic complications (MRI signal modifications with or without clinical manifestation) occurring within 4 months after the end of FSRT [14, 15], defined as the proportion of patients with at least one target brain metastasis with a bleeding complication within 4 months post-FSRT.

The efficacy endpoint is the local control rate of irradiated target lesions (all irradiated brain lesions with stable size or size increase less than 25%) 6 months after the end of FSRT, using RECIST 1.1 criteria.

Targets lesions correspond to all irradiated lesion regardless the presence of a bleeding signal.

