### Study treatment

Each targeted brain metastasis (hemorrhagic or not) will be treated at the dose of 30 Gy in 3 fractions at 10 Gy/fraction every 2 days [19, 20]. All target lesions (maximum 3 brain metastases plus one tumor bed) will be treated as much as possible over 1 week. However, cerebral irradiation of all the lesions may be spread over 7–10 calendar days. The irradiation facility could be LINAC (Truebeam STX®, Versa HD®, Novalis® …) or robotic radiosurgery system (Cyberknife®).

A minimum of 95% of the target volume (PTV) should receive at least 95% of the total prescribed dose of 30Gy (V95 > 28.5Gy).

The target volumes will be defined as [21, 22]:
GTV (Gross tumor volume): Gadolinium enhanced volume or surgical tumor bedCTV (clinical target volume) = [GTV + 1 mm]SM (set-up margins) = 1–2 mm according to the technique or irradiation system usedPTV (planning target volumes) = CTV + SM

Organ at risk will be delineated according to investigator habits (Optic chiasm, Optic nerves, Brainstem, Cochlea, Spinal Cord, Eyes). The prescription isodose percentage should be higher than 70%.

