- Cerebral MRI with T1 sequency Followed by Spectro-MRIe (ancillary study)	✓	✓ (in case of neurological degradation due to treated lesions)	✓	✓^b^	✓	✓	✓ ✓	
Quality of life questionnaires (EORTC QLQ C30 and BN20)	✓			✓ Only at 1 month	✓	✓	✓^d^	

^a^Creatinin must be performed before MRI

^b^4 weeks and 8 weeks after the end of irradiation (W4 and W8)

^c^Every 3 months up to at least one target irradiated lesion in disease progression

^d^only every 6 months

^e^Spectro-MRI is performed at the same time of standard cerebral MRI and only applies to patients who have given their signed consent

^f^After progression, a survival status will be collected every 3 months with persistent toxicities due to radiotherapy

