#### Brain tumor evaluation

Brain tumoral evaluation will be in line with international guidelines [23]. It will be based on a brain MRI performed at baseline (before FSRT), at 1 week, 4 weeks, 8 weeks after the end of FSRT and thereafter at 4 months, 6 months and every 3 months post-FSRT in the absence of tumoral progression.

Each brain MRI will include the following sequences [19, 24, 25]: T1, T2, T2*, T1 with gadolinium and T2 FLAIR, and, if possible, MRI SWI (susceptibility-weighted imaging).

Disease assessment evaluation will be determined locally according to RECIST version 1.1 criteria.

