### Statistical design overview

The study will be conducted in 2 steps (a ‘proof of concept’ step followed by a ‘validation’ step) with a two-stage phase 2 design proposed by Bryant and Day [13], combining both safety and efficacy as primary endpoint (Fig. 1).

We posited the following assumptions:
π_T0_ **≥** 0.15 and π_T1_ **≤** 0.05, the unacceptable and expected rate of hemorrhagic complications occurring within 4 months after the end of FSRT, respectivelyπ_R0_ **≤** 60% and π_R1_ **≥** 80%, the unacceptable and expected local control rate of irradiated target lesions at 6 months, respectively.

With an alpha risk of 10% for both the efficacy and the toxicity, and a power of 90%, a total of 41 assessable patients are required.

The continuation of the study will depend on the results of the interim analysis.

Interim analysis will be performed after the first step: 6 assessable patients will be analyzed. Inclusions will not be suspended during the interim analysis. If less than 3 patients are locally controlled at 6 months or if 2 or more patients have presented an intracerebral hemorrhagic toxicity within 4 months, then the study will be discontinued for futility. If 2 or more patients reported intracerebral hemorrhagic toxicity before the end of the first step, the study would be terminated early for excess of toxicity. Otherwise, the study could continue into the second step: 35 additional assessable patients will be needed.

Final analysis will be performed after the second step. After a 6-month follow-up of the 41 assessable patients, if less than 29 patients are locally controlled at 6 months, or if 2 or more patients had intracerebral hemorrhagic toxicity within the 4 months following FSRT, then the study will conclude that FSRT (3 x 10Gy over 1 week) is not indicated to treat patients with hemorrhagic brain metastases. Otherwise, that is, if 29 or more patients are locally controlled at 6 months and if 1 patient, at most, reported intracerebral hemorrhage within 4 months post-FSRT, then the study will conclude that FSRT is effective, well tolerated and does not increase intracerebral hemorrhagic toxicity in patients with bleeding brain metastases.

Considering a drop-out rate of 10% (lost to follow-up, protocol deviation, etc.), 7 and 39 patients will be enrolled in the first and second step, respectively, for a total of 46 patients.

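### The primary haemorrhage count opens only at the end of FSRT, so a bleed during the course falls outside it as worded; the bias is modest and cheap to remove

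*Protocol article*

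**What the plan says.** All references are to the protocol article.

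- **Abstract, Methods:** "Safety endpoint is defined as the rate of bleeding complications 4 months post-FSRT".
- **Primary objective:** the complication is one "occurring within 4 months after the end of FSRT". At patient level it is the proportion with "at least one target brain metastasis with a bleeding complication within 4 months post-FSRT". The event is defined by MRI signal change, with or without symptoms.
- **Statistical design overview, rates:** 15% and 5% are "the unacceptable and expected rate of hemorrhagic complications occurring within 4 months after the end of FSRT".
- **Statistical design overview, final rule:** the treatment is rejected "if 2 or more patients had intracerebral hemorrhagic toxicity within the 4 months following FSRT", so success allows at most one such patient in 41.
- **Statistical design overview, step 1:** a separate early stop applies when two or more patients have had haemorrhagic toxicity by the time step 1 is complete. It gives no starting point and does not mention the end of FSRT.
- **Study treatment:** the aim is to treat all lesions within about a week, but "cerebral irradiation of all the lesions may be spread over 7–10 calendar days".
- **Table 2:** during the irradiation week there is a weekly toxicity check, and an MRI only "in case of neurological degradation due to treated lesions".
- **Brain tumor evaluation:** MRI is "performed at baseline (before FSRT), at 1 week, 4 weeks, 8 weeks after the end of FSRT", then at 4 and 6 months and every 3 months.
- **Withdrawal from study:** intolerable toxicity is a listed reason for leaving.

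**The concern.** Up to three metastases and one tumour bed are treated in one course. A lesion can receive some or all of its fractions and bleed while others are still being treated. Table 2 foresees neurological deterioration in that period, yet a bleed found then precedes the window in every statement of the primary endpoint. It would be recorded under the secondary objective on acute and late toxicity, which does not enter the decision rule.

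The rules also do not match. An on-course bleed in step 1 could count towards the early stop and then not count at the final analysis.

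The trial exists because stereotactic irradiation is suspected of raising bleeding risk. Success would be reported as good tolerance with no increase in haemorrhagic toxicity. A count that leaves out the irradiation period can err in one direction only, towards that conclusion.

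**Working it through.** **Inputs from the article.** Rates of 5% (expected) and 15% (unacceptable) over 4 months after FSRT; 41 assessable patients; at most 1 event to pass; course length of 7–10 days.

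**Assumptions.** Four months = 122 days; constant hazard; every patient has a course of the stated length; every on-course bleed goes uncounted. The last two make the results upper bounds under constant hazard.

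**Step 1. The toxicity rule as written.** The limit is one event both at 6 and at 41 patients, so the two-stage pass probability equals the single-stage one:

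P(pass) = (1−p)^41 + 41·p·(1−p)^40

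- p = 0.05: 0.1221 + 0.2634 = 0.386
- p = 0.15: 0.0013 + 0.0092 = 0.0105

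The 0.386 does not agree with the stated 90% power. That is a separate matter and neither supports nor weakens this point.

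**Step 2. Share of events in the course.** With d course days the share is about d/(122 + d): 7/129 = 5.4% and 10/132 = 7.6%.

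**Step 3. Chance of at least one uncounted bleed in 41 patients.** Daily hazard h = −ln(1−p)/122; per-patient risk q = 1 − exp(−d·h); chance = 1 − (1−q)^41.

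| Post-FSRT rate | Course | q | Expected bleeds (41q) | Chance of at least one |
|---|---|---|---|---|
| 5% | 7 days | 0.0029 | 0.12 | 11% |
| 5% | 10 days | 0.0042 | 0.17 | 16% |
| 15% | 7 days | 0.0093 | 0.38 | 32% |
| 15% | 10 days | 0.0132 | 0.54 | 42% |

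Three fractions given every 2 days span about 5 days for one lesion. At d = 5 the chances are 8% and 24%.

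**Step 4. Effect on the decision.** Over 132 days the rate becomes p′ = 1 − (1−p)^(132/122).

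- p = 0.05: p′ = 0.0540; P(pass) = 0.1028 + 0.2404 = 0.343, against 0.386 as written.
- p = 0.15: p′ = 0.1612; P(pass) = 0.0007 + 0.0058 = 0.0066 (before rounding of the terms), against 0.0105 as written.

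**Step 5. If bleeds cluster in the course.** Here 15% is taken as the true rate over course and follow-up together, and a share f is assumed missed, so the counted rate is 0.15·(1−f).

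| f (assumed) | Counted rate | P(pass) |
|---|---|---|
| 0 | 0.150 | 1.05% |
| 5% | 0.1425 | 1.4% |
| 10% | 0.135 | 1.9% |
| 20% | 0.120 | 3.5% |
| 30% | 0.105 | 6.2% |

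Even at 30%, the chance of passing an unacceptable rate stays below the stated 10% alpha.

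**The case against.** The strongest reply is that most on-course bleeds would probably be scored anyway. The endpoint is a change in MRI signal, the comparison scan precedes FSRT, and the next scheduled scan is one week after the end. A silent bleed during the course would first appear on that scan, inside the window, and a symptomatic one would also differ from baseline if still visible. This stands as a likely reading. It is not secured, because no rule dates such a change and disease assessment is local, so two sites could score the same scan differently.

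A reader might also infer that patients whose course is stopped by a bleed are excluded. The article does not say so. The end of FSRT can be read as the last fraction given, and the withdrawal list does not remove anyone from the safety count. What stands is only that the article is silent on how they are counted.

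Third, on-course bleeds are not unwatched: there is a weekly toxicity check, a secondary toxicity objective, an IDMC and an early stop that could catch them. This answers the worry about patient oversight, but none of these feeds the final count.

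Finally, the 5% and 15% rates are defined for the post-FSRT window, so moving its start also touches the design rates. That is correct and belongs in the cost of the change.

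**Conclusion.** As worded, the primary safety endpoint, the design rates and the final rule leave the treatment course uncovered, and the step-1 early stop uses different wording. The bias is towards declaring safety and, at a constant hazard, modest: at most about 5–8% of events, a fall in pass probability of about 4 percentage points at 5% (0.386 − 0.343), and 0.4 points at 15% (0.0105 − 0.0066). The 11–16% and 32–42% chances of at least one uncounted bleed are upper bounds under that hazard.

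Two stronger readings are tempting and do not hold. One is that a single missed bleed changes the conclusion: it does so only when exactly one other patient's bleed is counted. The other is that the missed bleeds are the most frequent or most attributable ones: the article gives no data on timing within the course, so clustering remains an assumption.

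This is a worthwhile, low-cost correction of the primary endpoint's wording. It is not a flaw that undermines the design.

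**What to change.** Define the safety endpoint as haemorrhage from the first fraction until 4 months after the last fraction received, counted in every patient given at least one fraction, whether or not the course is completed. State that the week-1 MRI is scored against the pre-FSRT baseline. Use this same window in the step-1 interim rule, the step-1 early stop and the final rule.

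The change affects the endpoint sentence, the decision rules and the statement of the design rates. It adds no visits or imaging. The observed rate may be slightly higher, and the 5% and 15% rates should be stated to apply to the longer window. At a constant hazard and a 10-day course, 5% and 15% after FSRT correspond to 5.4% and 16.1% over the whole period, so the sponsor should say which is meant.

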#### Secondary objectives

The secondary objectives are to evaluate:
safety profile (all acute and late toxicities according to EORTC criteria)intra-cerebral progression-free survival (excluding irradiated lesions)extra-cerebral progression-free survivaloverall survivalquality of life evolution at short, mid and long term using EORTC QLQ-C30 and QLQ-BN20 questionnairessurvival without any toxicity (grade ≥ 2) including quality of life (QoL) impairment (of ≥10 points out of a 100-point scale in at least one dimension of QoL), nor tumor progression (Q-TWIST)the prevalence of modifications after FSRT on morphological, functional and spectro-MRI parameters

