**Fig. 2 Fig2:**
[figure not shown]
Schematic representation of the STEREO-HBM study. *Each targeted brain metastasis (hemorrhagic or not) will be treated at the dose of 30 Gy in 3 fractions at 10 Gy per fraction every 2 days. All target lesions (maximum 3 brain metastases plus one tumor bed) will be treated as much as possible over 1 week. However, cerebral irradiation of all the lesions may be spread over 7–10 calendar days. **Standard MRI imaging protocol plus optional multivoxel spectroscopy imaging (MSI) only for voluntary patients with specific signed informed consent. Abbreviation: FSRT hypofractionated stereotactic radiotherapy; MRI Magnetic Resonance Imaging. *Each targeted brain metastasis (hemorrhagic or not) will be treated at the dose of 30 Gy in 3 fractions at 10 Gy per fraction every 2 days. All target lesions (maximum 3 brain metastases plus one tumor bed) will be treated as much as possible over 1 week. However, cerebral irradiation of all the lesions may be spread over 7–10 calendar days. **Standard MRI imaging protocol plus optional multivoxel spectroscopy imaging (MSI) only for voluntary patients with specific signed informed consent. Abbreviation: FSRT hypofractionated stereotactic radiotherapy; MRI Magnetic Resonance Imaging

**Table 2 Tab2:** Table caption

	Before initiation of treatment D-15 to D0	Stereotactic irradiation week FSRT Treatment of all lesions in 7-10 days maximum	End of irradiation W1 (1 week after the end of irradiation)	Follow-up visits after treatment				Follow-up after progression^f^
				Each week up to 2 months after end of treatment W2 to W9	4 months after end of treatment W16	6 months after end of treatment W24	Every 3 months up to disease progression^c^	
Stereotactic irradiation		Each brain metastasis (hemorraghic or not) will be treated at 30 Gy in 3 fractions of 10 Gy / fraction every 2 days on maximum 7 days						
Signature of informed consent	✓							
Clinical exam including:								
- Disease medical history, weight, height, SC, PS) Patient pronostic (DS-GPA)	✓							
- Complete clinical evaluation and neurological examination		✓	✓	✓	✓	✓	✓	
- Evaluation of toxicities		✓(once a week)	✓	✓	✓	✓	✓	✓
Biological assessment^a^								
- Complete Blood Count	✓		✓	✓	✓	✓	✓	
- Creatinin-^**a**^	✓		✓	✓^b^	✓	✓	✓	
Imagery including:	✓							
- Cerebral scan	✓		✓	✓^b^	✓	✓		

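### Scheduled disease assessment ends at irradiated-lesion progression, which is not an event for the two secondary PFS endpoints, so later progression elsewhere goes unrecorded and both curves risk optimistic informative censoring

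*Protocol article*

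**What the plan says.** The Secondary objectives include "intra-cerebral progression-free survival (excluding irradiated lesions" and extra-cerebral progression-free survival. Both concern disease outside the treated lesions.

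The last scheduled-visit column of Table 2 carries note c: "Every 3 months up to at least one target irradiated lesion in disease progression". Note f describes what follows: "After progression, a survival status will be collected every 3 months with persistent toxicities due to radiotherapy". In the post-progression column the only tick is for toxicity evaluation; the clinical examination and imaging rows are empty.

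The section on brain tumor evaluation gives the MRI times and continues them "every 3 months post-FSRT in the absence of tumoral progression", without saying progression of what.

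The imaging rows of Table 2 are "Cerebral scan" and "Cerebral MRI with T1 sequency". A further row, "Complete clinical evaluation and neurological examination", is ticked from the irradiation week through the 3-monthly visits. The article gives no censoring rule for either PFS endpoint.

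**The concern.** Assessment for a time-to-event endpoint should run until that endpoint's own event, death or end of study. Here it ends at a different event. A patient whose irradiated lesion progresses at month 9 and who develops a new brain lesion at month 12 contributes no intra-cerebral progression, because nobody is asked to look for it or record it. The same holds for extracranial progression after local failure.

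Two things are at stake. Events are lost in a trial of 41 assessable patients. And if patients with local failure are also at higher risk of progression elsewhere, those who remain under observation are the better-risk ones and the curves look too favourable. This is a data-collection rule stated in the article, not an analysis detail that a later plan could settle.

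**Working it through.** The plan gives no PFS estimate, event count or power for these endpoints, so there is no stated figure to reproduce. The check has two parts.

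**1. Reading the schedule**

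| Question | Where | Answer |
|---|---|---|
| Is target progression an event for the two endpoints? | Secondary objectives | No |
| Which visits does note c govern? | Table 2 | Only the 3-monthly column after month 6; visits W1 to W24 carry no such condition |
| What is collected afterwards? | Table 2 note f | Survival status and persistent radiotherapy toxicities |
| What ends MRI in the text? | Brain tumor evaluation | Tumoral progression, site unspecified |

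The last row conflicts with note c. If any progression ends MRI, extracranial progression would also stop brain imaging. If only target progression does, it would not.

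**2. Size of the possible bias**

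From the plan: 6-month local control of 80% (expected) or 60% (unacceptable), and 41 assessable patients. So 20% to 40%, or 41 × 0.20 ≈ 8 to 41 × 0.40 ≈ 16 patients, would not be locally controlled at month 6.

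Assumed, because the plan gives no figure: 60% free of distant brain progression at 12 months before local failure; median survival 10 months, with deaths independent; distant hazard doubled after local failure.

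- Distant hazard h = −ln(0.60)/12 = 0.0426 per month.
- Local hazard λ = −ln(0.80)/6 = 0.0372, or −ln(0.60)/6 = 0.0851.
- Probability of surviving 12 months = exp(−12 × ln 2/10) = 0.435.
- True distant-progression-free probability: S(t) = exp(−(λ+h)t) + ∫₀ᵗ λ exp(−(λ+h)u) exp(−2h(t−u)) du. This gives S(6) = 0.756 and S(12) = 0.550 at 80% local control; 0.735 and 0.504 at 60%.
- True 12-month PFS = S(12) × 0.435 = 23.9% and 21.9%.

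The 12-month PFS reported under each reading, multiplying by 0.435 throughout:

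- *Censored at target progression, stop only after month 6:* S(6) × exp(−6h) × 0.435. This is 0.756 × 0.775 × 0.435 = 25.5% and 0.735 × 0.775 × 0.435 = 24.8%, so +1.5 and +2.9 points. At month 6 the bias is zero.
- *Censored at target progression, stop at any time:* 0.60 × 0.435 = 26.1%, so +2.2 and +4.2 points.
- *Imaging stops after month 6 but later deaths count:* [S(6) − exp(−6(λ+h)) × h/(λ+h) × (1 − exp(−6(λ+h)))] × 0.435. This is (0.756 − 0.126) × 0.435 = 27.4% and (0.735 − 0.083) × 0.435 = 28.4%, so +3.5 and +6.5 points.
- *Imaging stops at any time but later deaths count:* [1 − h/(λ+h) × (1 − exp(−12(λ+h)))] × 0.435 = 29.2% and 32.2%, so +5.3 and +10.2 points.

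If the distant hazard does not change after local failure, both censored versions have zero bias. The deaths-counted versions remain optimistic, because progressions before death are missed.

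A simulation with the protocol's MRI times let target progression, distant progression and death all be correlated (Gaussian copula, 400,000 patients per scenario; local control 80% or 60%, 12-month distant progression 40% or 60%, median survival 10 months). Overstatement of 12-month intra-cerebral PFS, in points:

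| Correlation | Censored, stop after month 6 | Censored, stop at any time | Imaging stops at any time, deaths count |
|---|---|---|---|
| 0 | 0 | 0 | 2.5 to 7.0 |
| 0.3 | 1.0 to 2.8 | 1.7 to 4.6 | 1.8 to 5.5 |
| 0.6 | 1.2 to 4.9 | 2.3 to 8.7 | 1.0 to 4.0 |

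Extra-cerebral PFS was not simulated. The mechanism is the same, but the article gives nothing from which to size it.

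**The case against.** A reader might infer that the two endpoints are informatively censored and will look too good. The article does not support that certainty. It states no censoring rule. Upward bias needs either positive dependence between local failure and progression elsewhere, or deaths counted after imaging has stopped. The dependence is plausible but undocumented: local failure may reflect lesion size or dose rather than systemic biology.

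A reader might also take all follow-up to end, with 8 to 16 of 41 patients lost by month 6. Survival and toxicity follow-up continue, and note c governs only the visits after month 6. An illustration without deaths (60% reported against a true 55% or 50%) would overstate the bias from plain censoring, since these endpoints count deaths.

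A third tempting reading is that extracranial disease is never assessed. Only body imaging is absent from Table 2. A complete clinical evaluation is scheduled, and a condensed article may leave body imaging to the full protocol, so its absence is not part of this point.

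The endpoints are also descriptive. Near a PFS of 25% with 41 patients, the standard error is about √(0.25 × 0.75/41) = 6.8 points, larger than most of the biases above. All of this stands. It limits the size and certainty of the point but does not answer it: the dates are not collected, for a reason irrelevant to the endpoints they serve.

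**Conclusion.** The point holds in limited form. After month 6, scheduled disease assessment stops at an event that is not an event for either secondary PFS endpoint, and progression at the relevant sites afterwards goes unrecorded. Both endpoints risk informative censoring, probably in the optimistic direction.

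Under the literal stop after month 6, with censoring at target progression, the overstatement of 12-month intra-cerebral PFS is 0 to about 5 points. An earlier stop raises it under positive dependence, to as much as 8.7 points in the simulated range. Counting later deaths while imaging has stopped usually raises it too, though at the strongest correlation simulated it gave less than plain censoring did. All sizes rest on assumed hazards, survival and dependence; only the local control range and the visit times come from the plan.

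The MRI stopping rule in the section on brain tumor evaluation and Table 2 note c must be reconciled. Only secondary endpoints are touched: the decision rule uses haemorrhage within 4 months and local control at 6 months. This is a cheap improvement, not a threat to the trial's main conclusion.

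**What to change.** Amend Table 2 note f so that, after target-lesion progression, the existing 3-monthly survival contact also records from routine-care imaging:

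- the date of first new or non-irradiated brain lesion progression;
- the date of extracranial progression;
- the date of last assessment for each.

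Continue until each endpoint's own event, and state that follow-up for these endpoints does not end at target-lesion progression. Align note c and the brain tumor evaluation section on which progression ends scheduled MRI.

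The cost is a few eCRF fields and an amended footnote, with no additional protocol scans. The downside is that routine-care assessments fall at less regular times, so progression dates after local failure will be less precise.

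If the dates cannot be collected, report distant brain or extracranial progression before local failure as a cumulative incidence, and label it so. That is a different estimand and does not recover PFS.
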